## Abstract

**Background:**

Standard surgical treatments for lower urinary tract symptoms (LUTS) due to benign prostatic obstruction (BPO) use a transurethral approach. Drawbacks are the need for general or spinal anesthesia and complications such as hematuria, strictures, and cloth retention. Therefore, a minimal invasive technique under local anesthesia is desired to improve patient safety. Recently, SoracteLite transperineal laser ablation (TPLA) has been introduced as a novel minimal invasive treatment for BPO. The system used is unique because 4 laser sources are independently available. This 1064-nm diode laser induces coagulative necrosis. Moreover, TPLA is unique because it has a transperineal approach and can be performed under local anesthesia in an outpatient setting.

**Objective:**

The primary objective of this study is to determine the safety and feasibility of TPLA treatment for men, who are fit for standard surgery, with LUTS due to BPO. The secondary objectives are to determine functional outcomes by flowmetry and patient-reported outcome measures (PROMs), side effects, and tissue changes observed on imaging.

**Methods:**

This study is a prospective, single center, interventional pilot study IDEAL framework stage 2a and will include 20 patients. Eligible patients are men ≥40 years of age, with a prostate volume of 30 to 120 cc, have urodynamically proven bladder outlet obstruction, and have a peak urinary flow of 5 to 15 mL per second. All patients will undergo TPLA of their prostate under local anesthesia by using the EchoLaser system. Depending on the prostate volume, 2 to 4 laser fibers will be placed bilaterally into the prostate. Patient follow-up consists of uroflowmetry, PROMs, and imaging by using contrast-enhanced ultrasound. Total follow-up is 12 months following treatment.

**Results:**

Presently, recruitment of patients is ongoing. Publication of first results is expected by early 2020.

**Conclusions:**

TPLA offers the potential to be a novel minimal invasive technique for treatment of LUTS due to BPO in men fit for standard desobstruction. This study will evaluate the safety and feasibility of TPLA and report on functional outcomes and tissue changes observed on imaging following TPLA treatment.

**International Registered Report Identifier (IRRID):**

DERR1-10.2196/15687

## Introduction

### Background

Lower urinary tract symptoms (LUTS) in men are mainly caused by benign prostatic hyperplasia. Cross-population prevalence of LUTS in men aged above 40 years is estimated at approximately 20% [1]. The incidence of LUTS due to benign prostatic obstruction (BPO) in the Dutch male population ranges from 3 per 1000 person years at ages 40 to 45 years to 38 per 1000 person years at ages 75 to 79 years [2]. LUTS have a major impact on quality of life compared with other chronic diseases [3,4].

Transurethral surgery is the most common procedure for prostate desobstruction. Numerous techniques have been developed over the years (eg, photo-vaporization and enucleation applying various modalities). The bipolar transurethral resection of the prostate (TURP) has favorable outcomes and a better short-term safety profile compared with monopolar TURP [5]. Photo-vaporization shows equal functional outcomes with a potentially better perioperative safety profile [5]. The holmium laser is the standard for enucleation and is associated with more favorable efficacy outcomes and less complications compared with monopolar TURP [5]. However, all techniques require anesthesia and hospitalization and induce retrograde ejaculation and complications such as hematuria and possible cloth retention while urethral and bladder neck strictures still occur.

Different minimal invasive techniques (eg, interstitial laser coagulation [ILC], transurethral microwave thermotherapy, and transurethral needle ablation) were developed that aimed for equivalent functional outcomes, although with shorter hospitalization, less use of anesthesia, and less complications [6]. Studies comparing these techniques with TURP showed improved patient safety profiles [6-9]. However, long-term functional outcomes were worse when compared with TURP, and the techniques are no longer advised by the guidelines [7,8].

Recently, new techniques (eg, Rezum and Aquablation) were developed. These techniques work with water vapor and waterjet ablation, respectively [10,11]. However, these techniques also use a transurethral approach resulting in similar complications such as hematuria, for example, 3 patients out of 15 for Aquablation [11]. Moreover, Aquablation requires general anesthesia [11]. As these techniques are still being investigated, they are not advised by the guidelines yet. Thus, transurethral surgical treatments are still advised by the guidelines, and there is no percutaneous technique for prostatic desobstruction, which is currently approved [12].

### SoracteLite Transperineal Laser Ablation

SoracteLite transperineal laser ablation (TPLA) of the prostate is a novel minimal invasive technique for LUTS treatment in men. Using a transperineal approach, up to 4 laser fibers can be positioned into the prostate by means of transrectal ultrasound guidance. TPLA generates light-induced thermal heating that results in coagulative necrosis around the laser fiber tip. TPLA requires only local anesthesia, and conscious sedation is optional. Hypothetically, the ablation is confined to the transition zone, respecting anatomical structures and potentially increasing the chance of preservation of antegrade ejaculation. However, as TPLA is a novel technique, only limited short-term outcomes are available. Patelli et al [13] demonstrated technical feasibility and safety of TPLA treatment and improvement of functional outcomes for patients unfit for TURP. Therefore, there is a need to study the safety and feasibility of TPLA treatment of men eligible for standard surgical treatments [13].

### Aim

The aim of this study is to prove safety and feasibility of TPLA treatment for men with BPO eligible for standard surgical treatment.

## Methods

### Study Objectives

The primary objective is to determine safety and feasibility of TPLA treatment for men with LUTS due to BPO and if fit for standard surgical treatment.

Secondary objectives are to determine (1) functional outcomes, (2) the possibility of spontaneous voiding immediately post-TPLA, (3) observation of side effects comprising hematuria, irritative voiding complaints, erectile function, and changes in ejaculation, and (4) evaluation of tissue changes by using contrast-enhanced ultrasound (CEUS).

### Outcomes

Feasibility is measured by technically successfully (without device-related adverse events) performed TPLA procedures. If 90% (18/20) of the treatments are successfully performed, we conclude that the treatment is feasible. Safety is assessed by the adverse events using the CTCAE version 5.0. TPLA is defined to be safe when ≤10% (2/20) of the patients experience adverse events of grade 3 or higher. For the secondary objectives, the functional outcomes are measured by uroflowmetry and International Prostate Symptom Score (IPSS) and erectile function by International Index of Erectile Function 15 (IIEF-15).

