Overall, 20 patients will be included in this study. This number is based on the IDEAL stage 2a recommendations for surgical innovations and past pilot studies [13-15].

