### Safety

The investigators will monitor patient safety. They can withdraw a patient from the study for medical reasons. In accordance to section 10, subsection 4, of the Wet Medisch-Wetenschappelijk Onderzoek met Mensen (medical research involving human subjects act in the Netherlands), the investigators will suspend the study if there is sufficient ground that continuation of the study will jeopardize patients’ health or safety. The investigators will notify the accredited institutional review board if this is the case. In case of an adverse event or serious adverse event, the responsible authorities will be informed.

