### Benefits and Risks

All patients included in this study have LUTS and have an indication for prostate desobstruction. This study aims to treat patients for their LUTS by TPLA to evaluate safety and feasibility and functional outcomes. The benefits focus on the minimal invasive character of TPLA and subsequent day care setting without clinical admission. Spinal or general anesthesia is made redundant by use of local anesthesia and optional conscious sedation.

Risks for patients focus on the procedure, subsequent device-related adverse events, and unknown long-term functional outcomes of the treatment. Needles are used to introduce fibers into the prostate, possibly causing damage and perforation of surrounding structures (eg, neurovascular bundle, urethra, or rectal wall). As ultrasound guidance is being used, these events are unlikely to occur. Hemorrhage, infection, fistula formation, sepsis, and death can occur. However, risks are expected to be low because the transperineal approach is already applied for biopsies of the prostate and has proven to be safe [24]. Furthermore, Patelli et al reported no procedure-related adverse events in 18 patients [13]. Therefore, risks of adverse events are minimal as described earlier.

Nonetheless, TPLA is a relatively new technique and long-term outcomes are unknown. Patelli et al described short-term functional outcomes demonstrating that the peak urinary flow rate improved from 7.6 to 13.3 mL per second at 3 months post-TPLA. Yet, studies that applied other minimal invasive LUTS treatments showed a reduction of long-term effectiveness and increase of retreatment rates over time [8,9]. Thus, when feasibility of TPLA in patients that are candidates for surgical desobstruction can be demonstrated, future studies will be able to focus on the long-term outcomes.

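### The safety verdict puts every event of grade 3 or higher into one allowance of 2 in 20, so it would still read safe if both events were related and life-threatening or fatal

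*Protocol article*

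**What the plan says.** Safety is half of the primary objective (Study Objectives). The Outcomes section names the scale, "Safety is assessed by the adverse events using the CTCAE version 5.0", and then gives the verdict: "TPLA is defined to be safe when ≤10% (2/20) of the patients experience adverse events of grade 3 or higher". The sample is fixed under Population and Sample Size: "Overall, 20 patients will be included in this study".

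Four other places bear on the point.

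- **Benefits and Risks** lists the harms foreseen: "Hemorrhage, infection, fistula formation, sepsis, and death can occur". It expects the risks to be low and cites an earlier TPLA series with no procedure-related adverse events in 18 men.
- **Safety** gives the investigators a duty based on judgement: "the investigators will suspend the study if there is sufficient ground that continuation of the study will jeopardize" patients' health or safety. It states no count or grade and does not refer to the definition of safe.
- **Outcomes**, on feasibility, asks for procedures free of device-related adverse events and is met at 18 of 20.
- **Data Analysis** says that adverse events are reported descriptively.

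**The concern.** The allowance of two was presumably set with severe but manageable events in mind. As worded, it covers everything from grade 3 to the top of the scale. Two men with a manageable grade 3 event and two men who die because of the procedure give the same count and the same verdict. The article does not argue that 10% is tolerable for the top grades, and its own account of risk points the other way: the men are fit for standard surgery, the risks are expected to be low, and the cited series had no related events.

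What is at stake is the wording of the primary conclusion. A prespecified verdict should not be one that the investigators would have to disown in the outcome where it matters most. The point is separate from the precision available with 20 men. It concerns what the two allowed events may be, and it would remain at any sample size with the same proportion.

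**Working it through.** **Inputs from the document.** n = 20; safe if at most 2 men have an event of grade 3 or higher; scale CTCAE version 5.0; no attribution clause in the safety rule.

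**Assumptions.** Grade 4 means life-threatening and grade 5 means death; this is the standard meaning of the named scale, which the article does not print. Men are independent. The true risks below are illustrative, because the document gives none beyond 0 of 18.

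**Step 1: the stated threshold.** 2/20 = 10.0%, which meets the ≤10% limit. 3/20 = 15.0%, which does not. The figure in the article is consistent.

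**Step 2: the literal consequence.** Suppose two men have related fatal events and no one else reaches grade 3. The count is 2, so the verdict is safe. The feasibility rule does not catch this either: two device-related deaths leave 18 of 20 procedures successful, which is a pass.

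**Step 3: behaviour if related grade 4-5 events are the only counted events.** Let s be the true risk per man.

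- Current rule passes: P(X ≤ 2) = (1−s)^20 + 20·s·(1−s)^19 + 190·s²·(1−s)^18.
- Added condition met (no such event): P(X = 0) = (1−s)^20.
- Safe with one or two such events observed: the difference between the two.

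| True risk s | Current rule passes | No such event | Safe with 1 or 2 such events |
|---|---|---|---|
| 1% | 99.9% | 81.8% | 18.1% |
| 2% | 99.3% | 66.8% | 32.5% |
| 5% | 92.5% | 35.8% | 56.6% |
| 10% | 67.7% | 12.2% | 55.5% |

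The case in which both allowed events are severe is the last term, 190·s²·(1−s)^18. It is 1.6% at s = 1%, 5.3% at 2%, 18.9% at 5% and 28.5% at 10%.

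**Step 4: other grade 3 events present.** Let g = 10% be the assumed share of men whose worst event is grade 3, with s = 5%.

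- Current rule passes: P(X ≤ 2 | 20, 0.15) = 0.0388 + 0.1368 + 0.2293 = 0.405.
- Passes with no severe event: 0.85^20 + 20·0.10·0.85^19 + 190·0.10²·0.85^18 = 0.0388 + 0.0912 + 0.1019 = 0.232.
- Safe with at least one severe event: 0.405 − 0.232 = 0.173.

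Once ordinary grade 3 events use up the allowance, the pass probability at s = 5% falls from 92.5% to 40.5%. The chance of a safe verdict with a severe event present falls from 56.6% to about 17%. The added condition would lower the pass probability further, from 40.5% to 23.2%.

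**The case against.** The strongest case on the other side has five parts.

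1. **This is a small pilot and a single severity cut-off is a clear choice.** That is fair. The rule contains no arithmetic error and does not contradict other text. But it is a complete definition with a number and a verdict, so its consequence follows from the wording and not from a detail left to a fuller document.

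2. **Two related deaths would very probably stop the study first, and descriptive reporting would show them.** Both are likely. A reader might infer that the trial has no safeguard against this outcome; the Safety section shows otherwise. Neither safeguard amends the definition of safe, however, and that is all this point claims.

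3. **Risks of 5% and 10% are far above what the article expects.** This stands. A reader might take 92.5% and 56.6% as the likely behaviour of the rule. They are not: they assume a high severe risk and no other counted events. At 1% the chance of two severe events is 1.6%, and Step 4 shows how quickly other grade 3 events shrink the figures.

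4. **The stricter rule has a price.** This stands too. With a true related grade 4-5 risk of only 1%, the added condition alone would withhold the verdict about 18% of the time; at 2%, about 33%. It also relies on a relatedness judgement by investigators who monitor safety themselves. The feasibility outcome already needs a judgement of device-relatedness, so the step is small, though relatedness to the procedure is slightly wider.

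5. **The safe label does not formally control later trials.** Correct. A reader might infer that it does because the Discussion places the pilot before large comparative studies. The text speaks only of initial data, and no section makes the label a condition for proceeding.

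**Conclusion.** The point holds as a defect in a stated decision rule. By its wording and simple arithmetic, the Outcomes definition returns safe with up to two related life-threatening or fatal events among 20 men, and no other section changes that verdict.

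The practical size is uncertain. If such events are rare, as the article expects, the anomalous verdict is unlikely: at an assumed 1% risk, the rule passes with one or two such events present 18.1% of the time, nearly always with one. At higher assumed risks it is common, up to 56.6% among the values tried, but only if no other grade 3 events occur. All these rates rest on assumed risks and on independence between men. The documents do not support describing the study as lacking safety oversight, or the label as a formal gate.

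The correction is worth making because it costs little and changes what the primary conclusion can mean.

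**What to change.** Keep the limit of 2 in 20 for events of grade 3 or higher. Add to the Outcomes section that safe is not concluded if any patient has a CTCAE grade 4-5 adverse event judged related to the device or procedure. Report the grade 3 or higher count by grade and relatedness beside the verdict.

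The Follow-Up section records adverse events by Clavien-Dindo whereas Outcomes uses CTCAE. The two should be reconciled so that the grades in the new sentence are defined.

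**Cost.** One sentence and a small table; no extra patients or visits. A relatedness judgement is needed for each grade 4-5 event, which extends the one already implied by the feasibility outcome. The real price is a stricter verdict: at assumed true risks of 1%, 2%, 5% and 10% the added condition is met with probability 82%, 67%, 36% and 12%. One related severe event would therefore remove the label even if TPLA is acceptable overall. The change affects the conclusion rule only, not the care of patients.

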### Study Design

This is a prospective, single center, interventional pilot study. Approval of the local medical ethical committee was obtained for the study protocol (registry number: NL66057.018.18). The study is in agreement with the IDEAL stage 2a recommendation [14].

### Population and Sample Size

Patients eligible for this study are men aged ≥40 years with proven bladder outlet obstruction by urodynamic investigation and a peak urinary flow of ≥5 mL per second to ≤15 mL per second, a postvoid residual of ≤250 mL, and a prostate volume of ≥30 and ≤120 cc. The inclusion and exclusion criteria are summarized in Textboxes 1 and 2.

Inclusion criteria.Male≥40 years of agePeak urinary flow: ≥5 mL per second to ≤15 mL per second, minimum voided volume of >125 mL, measured with uroflowmetryPostvoid residual: ≤250 mLProstate volume: ≥30 and ≤120 cc, measured by transrectal ultrasoundUrodynamically proven bladder outlet obstruction

Exclusion criteria.Previous invasive prostate interventionHistory of prostate or bladder cancerNo spontaneous voiding (eg, indwelling Foley catheter, clean intermittent catheterization, or suprapubic catheter)A clinical suspicion of prostate cancer based on:Abnormal digital rectal examinationUrologists’ judgment of the PSA level, preferably supported by a nomogram (eg, Prostaatwijzer version 3 with TRUS volume [16]) outcome with an indication for prostate biopsiesInability of temporary discontinuation of anticoagulation or antiplatelet therapyOther conditions/statusActive urinary tract infection/prostatitisMacroscopic hematuria without a known contributing factorPoor detrusor muscle function or other neurological disorder that would impact bladder function (eg, multiple sclerosis, Parkinson’s disease, spinal cord injuries, (diabetic) polyneuropathy)Concurrent malignancy except basal skin cancerHistory of pelvic radiation therapy or radical pelvic surgeryHistory of bladder neck contracture and/or urethral strictures within the 5 years before the informed consent dateBladder stonesMedical contraindication for undergoing TPLA surgery (eg, infection, coagulopathy, significant cardiac, or other medical risk factors for surgery)Diagnosed or suspected bleeding disorderContraindication for conscious sedation (eg, obstructive sleep apnea syndrome)

All patients will be recruited in the Amsterdam University Medical Centers, Academic Medical Center (Amsterdam, the Netherlands). Patients will be informed about this study in oral and written form. Patient approval is confirmed by signed informed consent. Patient inclusion has been summarized in a flow diagram (Figure 1).

Overall, 20 patients will be included in this study. This number is based on the IDEAL stage 2a recommendations for surgical innovations and past pilot studies [13-15].

**Figure 1 figure1:**
[figure not shown]
Flow diagram of the study design. LUTS: lower urinary tract symptoms; TPLA: transperineal laser ablation.

### Baseline Characteristics

Medical history and physical examination will be evaluated. In addition, IPSS and IIEF-15 will be used to measure voiding and erectile symptoms. Pain is measured by using a visual analogue scale (VAS), ranging from 0 to 10, and hematuria by the hematuria grading scale (HGS) [17]. Voiding characteristics and bladder function will be assessed by uroflowmetry with postvoid residual measurement and urodynamic investigation. Prostate volume measurement will be performed by transrectal ultrasound.

### Study Device

The TPLA treatment is performed using a diode laser system (SoracteLite, EchoLaser X4 system, Elesta; Figure 2). The system uses 4 diode laser sources, operating at 1064-nm wavelength, with a maximum energy of 7 watts continuous wave per source. The laser sources can be activated and configured individually (both separately and simultaneous), and the laser light is guided through a flexible quarts optical fiber.

The laser light induces tissue coagulation with a relatively deep penetration (up to 1 cm) because light of 1064 nm is poorly absorbed by hemoglobin and water [18]. However, fiber blood contact can lead to carbonization of the fiber tip, creating a black layer that partially absorbs the light [19]. Subsequently, the absorbed light is transformed into heat because of the black layer and other tissue constituents in the prostate. During TPLA, the prostate is continuously monitored by using transrectal ultrasound (MyLab Eight eXP, Esaote) with a biplanar probe (TRT33).

**Figure 2 figure2:**
[figure not shown]
The EchoLaser system with 4 fibers combined with the MyLab Eight eXP ultrasound device from Esaote (left) and the TRT33 probe with needle guide system (right).

### Study Procedure

The TPLA treatment will be performed by 2 urologists who followed a training to perform the TPLA procedure. TPLA treatment will be performed in an outpatient setting under local anesthesia. A single oral dose of ciprofloxacin 500 mg will be used as antibiotic prophylaxis. The patient will be placed in lithotomy position. A Foley catheter will be placed for urethral identification. The prostate will be visualized with a biplanar transrectal ultrasound probe. Pain management consists of local infiltrative anesthesia of the perineum with Lidocaine 2%, 5 to 10 mL, followed by an ultrasound-guided periprostatic block with Lidocaine 2%, 20 mL. On patients’ preference, conscious IV sedation with Midazolam 1 to 3 mg is offered. Depending on the prostate volume, 1 or 2 fibers will be placed transperineally in each side of the prostate in the transition zone by using ultrasound guidance and guiding needles (Figure 3 and Table 1). The fibers will be positioned parallel to the urethra while maintaining a minimal distance of 8 to 10 mm to the urethra and the rectal wall, and a distance of at least 15 mm to the bladder neck. A needle guide system will be used to support parallel placement of the needles. Following introduction of the optical fiber through the needle, the needle will be retracted for 10 mm, allowing exposure of the fiber tip and first 10 mm of the fiber to the tissue. When 2 fibers are located within the same lobe, the distance between the needles will be 10 or 15 mm, depending on the prostate size. If a median lobe is present, it will be treated by placing a needle and fiber as well.

Ablation will be performed with 3 watts per fiber and a total energy of 1800 J will be delivered per fiber in 600 seconds. Depending on the prostate volume, a pullback can be performed, retracting the fiber 1 cm along its trajectory to deliver another 1800 J (Table 1). When the treatment is completed, the Foley catheter will be removed. Dexamethasone 8 mg is administered intravenously postoperative to reduce edema and will be continued orally with the same dosage for 7 days.

